### 2.3. Randomization

Participants that were part of the MIDDEL trial were therefore randomized with their CHU to one of four groups: GMT, RCS, GMT plus RCS, or the control group. Randomization took place at the central study office after the completion of baseline assessments, using a computer-generated randomization list with a block size of four.

### 2.4. Intervention

A detailed description of the music interventions GMT and RCS were provided in the protocol article of the MIDDEL trial [1]. Care home units (CHUs) and their residents were randomly allocated to one of four arms: group music therapy (GMT), recreational choir singing (RCS), the combination of both music interventions, or the control group receiving care as usual. Each intervention was offered twice a week for three months and once a week during the following three months. Every session lasted approximately 45 min. GMT was provided in small groups (e.g., around five participants) by a qualified music therapist and included singing, improvising on instruments, and movement to music; RCS was provided in larger groups (e.g., with all residents of the unit) by a person with choir leading skills, and focused on singing. All units continued with standard care as locally available. The schedule, duration, and dose of intervention sessions are described in Figure 1.

### 2.5. Control Condition

The book reading served as a control condition for residents in the standard care group at T1 (within 1 month after completion of baseline assessment) and at T3 (3 months) and T6 (6 months). The control condition was similar to the music sessions in terms of group size, duration, and time of assessment. Hence, every book reading session took place around 15:00 h in the afternoon. All participating residents from the CHU participated in the book reading session. This session lasted 45 min. The book reading session was organized and supervised by either a volunteer, research assistant, research nurse, or care staff. This can also be the responsibility of one of the persons collecting samples before and after the session. The book reading session has an interactive character and functions as a social activity. A range of reading activities can be selected, such as reading local news stories, short stories, talking about headlines, and flipping through a magazine with pictures. Residents may read themselves or with the guidance of the supervisor if necessary. To illustrate, residents can read the paper and talk about headlines, whereas residents unable to read can flip through a magazine with pictures.

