Secondly, when collecting saliva samples, it is recommended to consider the sampling technique. The amount of saliva and SAA can be affected by the way samples are collected: stimulated samples by chewing on a small roll of cotton or unstimulated by passively drooling into a tube [5,53]. As the salivary flow rate can be limited in the target group because of aging and medication use, the use of a cotton roll (Salivette) was preferred. Another recommendation to better understand interactions is to include different types of biomarkers and multiple data collection time-points [15,16]. Ideally, cortisol concentrations are measured with a cortisol awakening response (CAR), with measurements up to seven times a day for two consecutive days. However, this is not the main question of this exploratory substudy; therefore, a more minimalistic design with three measurements on day one was chosen. Similar to other studies assessing changes in biomarkers in response to music (therapy) [46,54], in the current study, SC and SAA levels were assessed with multiple measurements, pre- and post-session. This will provide insight into changes within and between residents as a result of the music intervention.

Lastly, when designing a study assessing stress-related biomarkers, the timing of assessment, sampling periods, and consideration of psychobiological interactions should be taken into account [27]. Furthermore, an explanation of the bodily mechanisms of the biomarkers under investigation should be provided, thereby underlining the significance of testing these specific biomarkers [28]. Describing how the hormone is produced, how its levels are increased or decreased, and what its impact is on the body and the immune system is crucial to be able to put results and its relevance into perspective [28]. Moreover, the types of music should be clearly defined to be able to attribute changes in the biomarkers measured to a specific aspect of the music intervention, such as mode of delivery. This is the case in the music interventions offered in the MIDDEL trial.

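### Book reading does not match group music therapy on group size, and the T3 and T6 saliva contrasts set an established music activity against an occasional reading session

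*Protocol article*

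**What the plan says.** Section 2.5 (Control Condition) introduces the comparator: "The book reading served as a control condition for residents in the standard care group at T1", and again at T3 and T6. It describes reading sessions at no other time. It claims comparability with the music sessions: "The control condition was similar to the music sessions in terms of group size, duration, and time of assessment". The same section then says who attends: "All participating residents from the CHU participated in the book reading session". A reading session lasts 45 minutes and takes place at about 15:00.

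Section 2.4 (Intervention) gives the two music formats different sizes. For group music therapy: "GMT was provided in small groups (e.g., around five participants) by a qualified music therapist". For choir singing: "RCS was provided in larger groups (e.g., with all residents of the unit", closing the bracket there. Music is offered twice a week for three months and once a week for the next three, in sessions of about 45 minutes.

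Saliva and the stress Visual Analogue Scale (VAS) are taken before and 15 and 60 minutes after a session at T1, T3 and T6, in the GMT, RCS and control arms only (sections 2.6.3, 2.6.4 and 2.7). Of this pre- and post-session sampling, the Discussion says: "This will provide insight into changes within and between residents as a result of the music intervention".

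**The concern.** A matched control session lets the reader discount features that all sessions share, such as sitting in a group of a given size for 45 minutes in mid-afternoon. The article claims that match for group size, but its own descriptions do not bear it out for GMT.

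The session-matching sentence is also silent on exposure. By T3 and T6 a music resident has been offered many sessions of the sampled activity, while a control resident has had one or two. The outcome is acute stress. Whether a group event is routine or unusual could plausibly affect both the level before the session and the response after it. A difference between arms could then reflect familiarity as well as music.

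Attribution matters to this article. Section 2.1 leaves the combination arm out of saliva sampling partly to avoid doubt about which intervention caused an effect. Section 2.10.2 correlates the biomarker response at T3 and T6 with change in depression score, and those are the visits where exposure differs most.

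**Working it through.** **Group size.** Inputs: 8 units/80 participants in each of two countries and 4 units/40 in the third, 20% dropout, and an average cluster of eight after dropout (section 2.9); GMT groups of around five (section 2.4).

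- Participants per unit at baseline: 80/8 = 40/4 = 10. The Conclusions give the same ratio for the main trial, 1000/100 = 10.
- After 20% dropout: 10 × 0.8 = 8, which reproduces the article's cluster size.
- At the lower recruitment target of 180 in 20 units: 180/20 = 9 at baseline and 9 × 0.8 = 7.2 after dropout.
- Reading group relative to GMT: 10/5 = 2 at baseline and 8/5 = 1.6 after dropout, if GMT groups stay at about five.
- Relative to RCS: if all residents of a unit sing, the choir is at least as large as the reading group. How much larger cannot be computed, because unit size is not given.

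One reading format cannot be similar in size both to a group of about five and to a markedly larger one. The mismatch is clear for GMT and undetermined for RCS.

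**Exposure.** Take three months as 13 weeks (assumption) and count sessions offered, not attended.

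- Music by T3: 2 × 13 = 26.
- Music by T6: 26 + 1 × 13 = 39.
- Music before T1: T1 may fall anywhere in the first month, so from 0 up to about 2 × 4 = 8.
- Reading: T1, T3 and T6 are the first, second and third sessions described.

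| Visit | Music sessions offered by then | Earlier reading sessions |
|---|---|---|
| T1 | 0 to about 8 | 0 |
| T3 | about 26 | 1 |
| T6 | about 39 | 2 |

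The gap is smallest at T1 and grows with each visit. A change in the music-versus-reading difference from T1 to T6 could therefore reflect growing familiarity with the music sessions.

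**What is matched.** Duration (45 minutes against about 45) and clock time (reading at about 15:00; sampled sessions preferably at 15:00) agree, and those parts of the claim can stay.

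**The case against.** The other side has several fair points.

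- The article says similar, not equal, and gives both music group sizes as examples. It refers to the main trial's protocol for detail that is not shown here. This softens the conflict and leaves the RCS comparison open. It does not make a session for all participating residents similar to a group of about five.
- The study question concerns repeated music interventions, so a regular group and routine are part of what is delivered. That is right, and it is how the result should be worded: the package as delivered against occasional reading, not the effect of music as such.
- The Discussion sentence promises insight, not isolation of a cause. It is mild, but it still names the music intervention as the source of the changes.
- Saliva and VAS outcomes are secondary, and their effects are largely to be described. This limits the weight of the point.
- Regular reading groups would equalise exposure but would change the care-as-usual arm on which the longer-term comparisons rest. The article does not give this as its reason, but occasional reading is a defensible compromise.

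A reader might go further than the text allows in three ways. One is to infer that leaders differ in familiarity to the disadvantage of reading. Reading may be led by care staff whom residents could know well, and a music therapist or choir leader may be new at first, so this can run either way. Another is to treat T1 as a visit with equal familiarity. T1 can follow up to about eight music sessions, and equality at a first session is not shown either. A third is to conclude that the hair cortisol and PSS-10 results are compromised. Section 2.11 does name the control as usual care or book reading, but those longer-term comparisons do not depend on a matched reading session.

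**Conclusion.** The group-size part of the matching claim is not supported by the article's own descriptions. It fails for GMT, where reading groups are about 1.6 to 2 times as large, and it cannot be judged for RCS. At T3 and T6 the music-versus-reading contrasts compare an activity offered about 26 and 39 times with one held once or twice before. They cannot isolate music from familiarity or, for GMT, from group size.

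A reader might infer that these contrasts are biased in a known direction or are uninformative. The documents do not support that: neither direction nor size can be derived from them, and the contrasts remain valid as comparisons of what was delivered.

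The conclusion rests on three assumptions: 13-week quarters, offered sessions standing in for attended ones, and about ten participating residents per unit, all of whom come to reading as stated. It concerns secondary, exploratory outcomes only, and the co-primary comparisons are unaffected.

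**What to change.** 1. Reconcile sections 2.4 and 2.5 by removing group size from the matching statement. Keep duration and time of day.
2. Describe the immediate-effect contrasts as music sessions as delivered versus an occasional reading session, and bring the attribution sentence in the Discussion into line.
3. Report the number of prior sessions attended and the group size at the sampled session, by arm and visit.

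Two larger changes may seem attractive but are not recommended. Making a first-session T1 the main contrast would move away from repeated intervention and from the planned T3 and T6 correlations. Relying on GMT versus RCS instead would bring in a group-size difference of its own, about five against possibly a whole unit.

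The cost is mainly wording. No samples or sessions are added. Attendance and group size need to be on record, and the data availability statement says data are still to be collected. The downside is a narrower conclusion for the saliva and VAS outcomes.

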### 2.6. Outcome Measures

#### 2.6.1. Co-Primary Study Parameters: Hair Cortisol

Repeated assessment of HC is needed to assess the effect of repeated music interventions on chronic stress. HC provides insight into the amount of accumulated cortisol over a certain period (e.g., 1 or 3 months). Hair samples were collected at baseline (T0), at 3 months (T3), at 6 months (T6), and after 12 months (T12).

#### 2.6.2. Co-Primary Study Parameters: Perceived Stress Scale

Information from HC was complemented with subjectively experienced stress using the 10-item Perceived Stress Scale (PSS-10) [33]. This is a reliable and valid questionnaire that can be filled out by the resident or by proxy [34]. Stress experienced in the past month and feeling in control in stressful situations was assessed. The original questionnaire contains 14 items; however, the use of the 10-item version is recommended [35]. A higher sum score indicates higher perceived stress. Chronic stress was assessed with the PSS-10 at the same time as the hair samples were collected.

#### 2.6.3. Secondary Study Parameters: Salivary Cortisol and Alpha-Amylase

SC can provide more insight into how well the endocrine stress system responds to an immediate intervention because HC does not provide insight into how well the HPA axis functions. As residents with depressive symptoms were expected to have steeper cortisol slopes, we hypothesized that participants have a higher SC before the start of the music session, and participating in the music intervention attenuates the SC. Samples were collected on days a music or book reading session took place, between 12.00 and 17.00 h, preferably at 15.00 h, to minimize any confounding effects of the diurnal hormonal rhythm. In order to assess the immediate effects of music interventions on stress, saliva samples were collected to assess SC and SAA levels just before, 15 min after, and 60 min after the music/book reading session. Multiple measurements of SC and SAA per resident were required because of variations in levels over time within residents [15]. The assessment took place at T1 (within 1 month after the music interventions started or within 1 month after completion of the baseline assessment in the control group), T3 (3 months), and T6 (6 months). The days were selected according to logistic convenience (the first session that took around 15.00 h around T1, T3, and T6 were selected).

#### 2.6.4. Secondary Study Parameters: Proxy- or Self-Reported Experienced Stress

On days when saliva samples are collected, residents or a proxy reported any experienced stress using a Stress Visual Analogue Scale (VAS). The VAS is a vertical line of 100 mm with endpoints labeled ‘The least stress you can imagine’ (0) and ‘The most stress you can imagine’ (100). Residents or their proxies were asked to indicate on this line how stressed they felt at that exact moment. The scale thereby provides a single score between 0 and 100, representing subjective stress [36]. The VAS was filled out at T1, T3, and T6. Similar to the collection of saliva samples, the VAS was filled out—by proxy if necessary—just before, 15 min, and 60 min after the music or book reading session.

### 2.7. Data Collection Procedures

Biomarkers were collected throughout the trial to assess the immediate and longer-term effects of repeated music interventions on chronic and immediate stress in care home residents with dementia and depressive symptoms (Figure 2). In Figure 2, the stress assessments of the substudy are presented within the assessment schedule of the MIDDEL trial. Hair samples were collected in all groups at T0, T3, T6, and T12 to assess physiological changes in chronic stress. Saliva samples were collected in the RCS, the GMT, and the control group at T1, T3, and T6. Saliva samples were collected just before, 15 min, and 1 h after the intervention to assess the immediate intervention effects. The group GMT plus RCS were only included to assess the longer-term effect of repeated music intervention on (chronic) stress.

#### 2.7.1. Hair Sample Collection

In order to collect hair samples, research nurses cut hair samples of at least 3 to 4 cm long in all eligible residents at T0, T3, T6, and T12. Several thin hair strands were cut as close as possible to the scalp from the posterior vertex region of the head. A short questionnaire was filled out to assess hair characteristics. The University of Vienna developed detailed Standard Operating Procedures (SOPs) to ensure data collection takes place in the same manner in the three participating countries.

#### 2.7.2. Saliva Sample Collection

Residents were asked to collect the saliva using longer-length Salivettes (Salivettes, Sarstedt, Sevelen, Switzerland) and small cotton rolls originally devised for infants and young children, and the swab could be held by the research nurse, who was assisting with the sample collection. Although the use of Salivettes is not optimal to assess SAA, after careful consideration, we choose the use of longer-length Salivettes (SalivaBio Children’s Swab method) over the use of a passive drooling technique, as this was expected to be safe (eliminate the risk of ingestion), feasible, easy to learn and perform, and clean [20]. Hereby, we also took into account our expectation that a proportion of participating care home residents with dementia and depressive symptoms have difficulty understanding instructions and experience dry mouth due to age and medication use. Care staff received instructions prior to the day of sample collection, asking them to help residents—where possible—avoid physical exercise and chewing gum (24 h); consuming caffeinated and alcoholic beverages, juice, and tobacco (18 h); psychotropic drugs (6 h); brushing teeth; and eating or drinking (1 h) before the collection of the saliva sample. A short questionnaire was filled out by the proxy (care staff) to assess adherence to instructions prior to sample collection. Prior to the first collection of saliva samples (T1), residents practiced the saliva collection procedure when necessary to become familiar with the process.

There are different procedures to collect the saliva sample with the Salivette. It is recommended to keep the technique (stimulated or unstimulated) and location in the mouth similar across the study and residents because these affect the type of glands that produce the α-amylase that are activated and the amount of amylase that is secreted [20]. Saliva composition can differ significantly between stimulated and unstimulated saliva collected samples [37]. Several studies applied saliva sample collection methods in care home residents with dementia. Both unstimulated and stimulated saliva sample collection were applied previously in dementia research [38,39,40,41,42,43,44]. In some studies, specific saliva collection methods are not described in detail [45,46,47]. Mixed methods were applied when unstimulated collection did not lead to sufficient saliva to collect [37]. The current literature does not favor one method over the other. Hence, in the specific population of the current study, feasibility was the main selection criterion. The procedures to collect saliva samples in participating residents were carefully considered and pilot tested to assess which method is more appropriate. The saliva collection protocol applied in the current study is similar to methods applied by Pu et al. (2020), aiming at unstimulated saliva collection [42]. Where needed, mixed methods were applied. Residents were asked to either keep the roll in their mouth for approximately 2 min without chewing (thereby collecting unstimulated saliva) or, if needed, to softly chew on the roll for approximately 1 to 2 min (thereby collecting stimulated saliva). The roll was placed into a small tube and stored at −20 °C before analysis took place. Where possible, all samples of the same resident were assayed in the same batch, and SAA was assessed on the same day as SC.

### 2.8. Biochemical Analyses

Biochemical analyses of hair and saliva samples were performed at the biochemical laboratory of the University of Vienna. The University of Vienna conducted the analyses of biomarkers, α-amylase and cortisol from saliva samples and cortisol from hair samples. For determination of HC concentration in hair samples, the first scalp-near 3 cm segment was used, which is thought to reflect the cumulative cortisol secretion of the past 3 months [48]. Hair wash and cortisol extraction procedures were based on a previously established laboratory protocol [49]. In brief, hair samples were washed twice for 3 min using 3 mL isopropanol. For cortisol extraction, 10 ± 0.5 mg (alternatively, 7.5 ± 0.5 mg, dependent on the sufficient amount of hair provided across the participants’ sample) of whole, finely cut hair was incubated in 1.8 mL methanol for 18 h at room temperature. After incubation, 1.6 mL was transferred to another glass vial. Then, 1.6 mL of the supernatant was evaporated at 50 °C until samples were completely dried. Finally, the samples were re-suspended with 225 µL ultra-pure water and vortexed for 20 s. For cortisol determination, commercially available cortisol luminescence immunoassay was used (LIA, IBL, Hamburg, Germany). Saliva samples were stored at −20 °C until analysis. Free cortisol concentration in saliva was determined by using a commercial luminescence immunosorbent assay (LUM; IBL, Hamburg, Germany). SAA activity was measured using an enzymatic colorimetric test [50] and reagents obtained from DiaSys Diagnostic Systems (Holzheim, Germany). Saliva was diluted at 1:625 using 0.9% saline solution. The reagents contain the enzyme α-amylase in a specified amount and alpha-glucosidase, which converts the substrate ethyliden nitrophenylto p-nitrophenol. The rate of formation of p-nitrophenol was directly proportional to the samples’ amylase activity and was detected using an absorbance reader at 405 nm (Biotek Synergy HTX, Biotek Instruments, Winooski, VA, USA). Inter- and intra-assay coefficients of variation were calculated to assess precision of the analytic method and were expected to be below 10% for all assays. All samples of one subject were analyzed in the same batch, if possible, to reduce error in variance. Saliva samples with an insufficient amount of saliva to analyze were excluded from statistical analysis.

### 2.9. Sample Size and Power

Through convenience sampling, a subsample of residents from three countries (the Netherlands, Germany, and Norway) from the MIDDEL trial was asked to participate in this substudy. The aim was to include 50 care home residents in every group (GMT, RCS, GMT plus RCS, control group at baseline). The Netherlands and Germany aimed to include 8 CHUs/80 participants each, and Norway aimed to include 4 CHUs/40 residents. Attrition of residents was expected to occur due to mortality, moving to another care home, or refraining from participation in the substudy. The mean length of stay in a care home in the Netherlands is 8 to 12 months. A mortality rate of 20% within the intervention period of 6 months (primary outcome at 6 months) was taken into account with respect to the sample size. Mortality is lower in care home residents with mild to moderately severe dementia (compared to severe and very severe). The power for this exploratory substudy with this given sample size was difficult to determine because there are no previous studies or agreed minimal clinically important difference for this combination of intervention, population, and outcome. As in the MIDDEL protocol [1], the main effects in this substudy were tested as GMT versus no GMT and RCS versus no RCS so that all participants with available data could be used in each test. Thus, after a dropout of 20% until the primary endpoint of 6 months, as assumed in the MIDDEL protocol, we expected to have 160 participants in total. Compared to the MADRS, we expected the cluster effect in these biological indicators to be smaller, with an ICC ≤ 0.01. The average cluster size after 20% dropout will be eight. Because there are two main comparisons, tests were Bonferroni-corrected from 5% to 2.5%, two-sided. We used R to determine the effect size for which 80% power is reached with a two-sample *t*-test with 160 participants in total, adjusted for clustering, with a two-sided 2.5% significance level, and found that the effect size that can be reliably determined with this substudy is d = 0.51, i.e., a medium effect size [51]. This seems reasonable compared to previous studies of music therapy [14,52]. The actual power may be higher in a longitudinal model if time points are correlated.

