### 2.10. Data Analysis

#### 2.10.1. Co-Primary Study Parameters

Stress (HC concentrations and perceived stress measured with the PSS-10) after 3 and 6 months was modeled to account for differences in therapy (RCS compared to no RCS, GMT compared to no GMT, additional effects of GMT + RCS combined, and baseline differences in stress (HC concentrations and perceived stress measured with the PSS-10) (T0).

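### The Bonferroni split covers the two treatment contrasts but not the two co-primary outcomes, no success rule is given, and the detectable effect of d = 0.51 has no basis for PSS-10

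*Protocol article*

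**What the plan says.** All references are to the protocol article.

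- **Contrasts and alpha (section 2.9).** "the main effects in this substudy were tested as GMT versus no GMT and RCS versus no RCS", and "Because there are two main comparisons, tests were Bonferroni-corrected from 5% to 2.5%, two-sided".
- **Power (section 2.9).** The calculation looks for "the effect size for which 80% power is reached" in a two-sample t-test "with 160 participants in total, adjusted for clustering, with a two-sided 2.5% significance level". Its result is that "the effect size that can be reliably determined with this substudy is d = 0.51".
- **Clustering (section 2.9).** Relative to the MADRS, "we expected the cluster effect in these biological indicators to be smaller, with an ICC" of at most 0.01. The average cluster size after dropout is eight.
- **Time point (section 2.9).** The primary endpoint is placed at 6 months, and the 160 participants are those expected to remain then.
- **Outcomes (sections 2.6.1 and 2.6.2).** Hair cortisol is headed as co-primary, and so is the questionnaire: "Co-Primary Study Parameters: Perceived Stress Scale". PSS-10 may be completed by the resident or by a proxy.
- **Model (section 2.10.1).** "Stress (HC concentrations and perceived stress measured with the PSS-10) after 3 and 6 months was modeled", with the two treatment contrasts, their combination and baseline stress as terms.
- **Claim (section 4, Conclusions).** The study is said to have enough power for relevant effects on both biological and psychological measures of chronic stress.

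The article does not say whether a positive finding requires one co-primary outcome or both.

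**The concern.** The plan commits itself to familywise control and gives its reason, which is a count of two. That count includes the treatment contrasts and leaves out the second co-primary outcome. Two contrasts on two outcomes make four primary tests, each at 2.5%. Depending on the success rule, either the 5% error rate or the 80% power is then not what section 2.9 says. A benefit seen on only one of the two outcomes could be reported as Bonferroni-controlled at nearly twice the stated error.

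The second gap concerns PSS-10 itself. The small ICC is argued from the biological nature of the outcome, and that argument does not reach a questionnaire that staff or relatives may complete. The Conclusions nevertheless extend the power claim to psychological measures.

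**Working it through.** **Inputs from section 2.9.** N = 160 after dropout, so 80 against 80 per contrast; cluster size 8; ICC 0.01; two-sided alpha 0.025 per test; 80% power. **Assumed, because the article gives no values:** the correlation between the two outcomes (0 to 0.5 and beyond) and the ICC of PSS-10 (0.02, 0.05, 0.10).

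**1. The plan's own figure.**
- Design effect = 1 + (8 − 1) × 0.01 = 1.07.
- Effective n per side = 80 / 1.07 = 74.8.
- Solving the two-sample t-test (noncentral t, df = 2n − 2) for 80% power at alpha 0.025 gives d = 0.509. Power at d = 0.51 is 80.2%.

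The stated d = 0.51 reproduces for one contrast on one outcome with ICC 0.01.

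**2. If success on either outcome counts.** Familywise error with each test at 2.5%:
- The two tests counted in the plan: 1 − 0.975² = 4.9%.
- Four tests, all independent: 1 − 0.975⁴ = 9.6% (Bonferroni bound 4 × 2.5% = 10%).
- Four tests, contrasts independent and outcomes correlated 0.5 (assumed): about 9.1%.

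Restoring 5% needs 5% / 4 = 1.25% per test. With n = 74.8 per side, the t-test then gives d = 0.552 at 80% power, and power at d = 0.51 is 72%.

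**3. If both outcomes must succeed.** No further split of alpha is needed, because a false claim on a contrast requires a significant result on the outcome with no effect, at 2.5%. The power figure changes instead. With 80% power on each outcome at d = 0.51, joint power per contrast is:

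| Assumed correlation of the two test statistics | Joint power |
|---|---|
| 0 | 0.80² = 64% |
| 0.5 | 69% (bivariate normal) |
| approaching 1 | approaching 80% |

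These values grant PSS-10 the ICC of 0.01, so they are favourable.

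**4. PSS-10 on its own.** Same t-test, alpha 2.5%:

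| Assumed ICC | Design effect | Effective n per side | Detectable d | Power at 0.51 |
|---|---|---|---|---|
| 0.02 | 1.14 | 70.2 | 0.53 | 77% |
| 0.05 | 1.35 | 59.3 | 0.57 | 69% |
| 0.10 | 1.70 | 47.1 | 0.64 | 58% |

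**The case against.** **The study is exploratory, and section 2.9 admits that power was hard to determine.** This is true and it softens the consequence. But the article still names co-primary outcomes, states a Bonferroni rule with its reason, and concludes that power is adequate. Those statements should agree with each other.

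**A success rule can be left to the analysis plan.** Often it can. The point here is that a correction is stated, with a count that does not match the outcomes named in sections 2.6.1, 2.6.2 and 2.10.1.

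**The planned analysis is more efficient than a t-test.** This stands in part. Section 2.10.1 includes baseline stress, and section 2.9 notes that a longitudinal model may have more power. With an assumed baseline–outcome correlation of 0.4, 0.552 × √(1 − 0.16) = 0.51, which cancels the loss from the stricter alpha; 0.3 gives 0.53 and 0.5 gives 0.48. So 0.55 and 72% are figures on the plan's own t-test basis, not forecasts for the final model. The gain does nothing for the error rate.

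**Stronger readings that the article does not support.**
- A reader might count both time points and reach eight tests, with familywise error up to 1 − 0.975⁸ = 18.3%. Section 2.9 names 6 months as the primary endpoint, and nothing says that 3 months is tested separately as primary. Four is the supported count.
- A reader might conclude that neither the 5% nor d = 0.51 holds. That merges two alternative success rules: under either-suffices the 5% fails, while under both-required it holds and the power statement fails.
- A reader might call d = 0.51 wrong for PSS-10. No ICC for PSS-10 or for the MADRS is given. One carer rating several residents is plausible but not stated, and at an ICC of 0.02 the detectable effect is only 0.53.

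**Conclusion.** The point holds in limited form. With two co-primary outcomes and no success rule, the 5% familywise error and the 80% power of section 2.9 cannot both stand as written unless the two outcomes are almost perfectly correlated.

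- Either outcome suffices: the error rate is nearly double the stated 5%, and correcting it costs a modest 0.04 in detectable d (0.51 to 0.55).
- Both are required: the error rate is as stated, and joint power per contrast falls short of 80% by about 11 to 16 percentage points for correlations between 0.5 and 0.

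The arithmetic behind d = 0.51 is right for a single contrast on hair cortisol. For PSS-10 the figure has no stated basis, so the power claim in the Conclusions goes further than the calculation. The results rest on four tests at 6 months, the plan's t-test with its design effect, and the assumed correlations and PSS-10 ICCs shown above.

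**What to change.** Repeat in section 2.10.1 that 6 months is the primary time point, and state the success rule. Then choose one of:

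1. **Both co-primary, either sufficing.** Test each contrast on each outcome at 1.25% and restate the detectable effect for hair cortisol as d = 0.55.
2. **Both co-primary, both required.** Keep 2.5% per contrast and report joint power with its assumed correlation in place of 80%.
3. **Hair cortisol as the single primary outcome.** Keep 2.5% per contrast and d = 0.51, and move PSS-10 to secondary. The hypothesis in the Introduction is already worded for hair cortisol alone.

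In every case, give PSS-10 its own ICC, with a source or a range, and its own detectable effect; otherwise limit the power claim in the Conclusions to hair cortisol.

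No extra participants or samples are needed. The cost is a slightly less favourable stated figure under options 1 and 2, or a lower rank for PSS-10 under option 3. Option 3 changes the outcome hierarchy, so it should be recorded as such.
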